## Exclusion

Exclusion criteria are as follows: (1) Received rituximab or any other B-cell depletion therapy within 24 weeks before screening, or received biologics or small-molecule targeted drugs for immune-related diseases (such as abatacept, infliximab, adalimumab, golimumab, belimumab, tocilizumab, or JAK inhibitors) within 4 weeks before screening, except for herpes zoster vaccine; (2) Received plasma exchange or immunoadsorption therapy within 12 weeks before screening; (3) Prior ineffective or intolerant use of mycophenolate mofetil; (4) Patients with autoimmune diseases other than SLE, including dermatomyositis/polymyositis, mixed connective tissue disease, systemic sclerosis, rheumatoid arthritis, etc., except for patients with secondary Sjögren's syndrome who are allowed to participate in the trial; (5) Blood abnormalities at screening, including any of the following: WBC < 2000/μL, Hb < 6g/dL, PLT < 30000/μL. If any of these abnormalities occur, a repeat screening may be performed, and if the subject meets the inclusion criteria, they can be considered eligible for inclusion; (6) Severe liver or renal impairment at screening, with any of the following abnormalities: total bilirubin > 1.5 times the upper limit of normal (ULN), alkaline phosphatase > 2 ULN, ALT or AST > 2 ULN, eGFR < 30 ml/min or serum creatinine > 265.2 μmol/L. If any of these abnormalities occur, a repeat screening may be performed, and if the subject meets the inclusion criteria, they can be considered eligible for inclusion; (7) Severe uncontrolled cardiovascular disease, neurological disorders, pulmonary diseases (including obstructive lung disease and interstitial lung disease), liver disease, endocrine disorders (including uncontrolled diabetes), or gastrointestinal diseases; (8) Current or recent (within 4 weeks before randomization) severe active or recurrent bacterial, viral, fungal, parasitic, or other infections (including but not limited to tuberculosis and atypical mycobacterial diseases, hepatitis B and C, HIV infection, herpes zoster), or requiring hospitalization and intravenous antibiotic treatment during the screening period; (9) Underwent major surgery within 12 weeks before screening or expected to undergo major surgery during the study period, which is considered to pose unacceptable risks to the patient; (10) Received live vaccines within 12 weeks before randomization or anticipated to receive/require live vaccines during the study period, excluding herpes zoster vaccine; (11) History of malignancies, including solid tumors and hematological malignancies (except for treated and cured); (12) Pregnancy or breastfeeding; (13) If the patients are of reproductive age and do not consent to using effective contraception during the trial.

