## Subjects Eligibility

Recruitment methodologies include advertisements in academic media as well as liaisons with general practitioners, rheumatologist.

Inclusion criteria are as follows:

(1) Patients with a documented history of fulfilling at least 4 out of the 11 ACR 1997 SLE classification criteria before randomization; (2) Age between 18 and 65 years at the time of obtaining informed consent; (3) Biopsy-confirmed lupus nephritis with pathological classification of Class III, IV, V, III+V or IV+V (2003 ISN/RPS lupus nephritis histological classification criteria), accompanied by active lesions (activity index ≥ 1 and/or increased chronicity index), within 24 weeks; (4) Urine protein/creatinine ratio > 1.0 or 24-hour urine protein quantification > 1.0 g, with or without active urinary sediment containing red blood cell casts; (5) All subjects receiving concurrent treatment with steroids alone or in combination with antimalarial drugs; (6) Meeting one of the following conditions: a. Never received immunosuppressive agents previously. b. Previously received immunosuppressive agents (including CTX, cyclosporine, TAC, MMF, azathioprine, leflunomide, or sirolimus) but had inadequate response or intolerance to treatment; (7) For women of childbearing potential, a negative serum pregnancy test at screening; (8) Willingness to provide written informed consent and comply with the study protocol requirements and restrictions.

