
## Intervention

In this study, the intervention factor is UC-MSCs. The UC-MSCs used in the study will be produced by Jiangsu Renocell Biotech Co., Ltd. that conforms to Good Manufacturing Practice standards. UC-MSCs at passages 4 will be utilized, and the transplantation dose will be 2 × 10^6^ /kg cells based on our preclinical study results. To ensure sterility and viability, UC-MSCs will be suspended in 30mL of sterile normal saline and stored at approximately 4 °C during transportation. The stem cell suspensions will be transported as quickly as possible to enable infusion within 12 hours of dissociation. Throughout the six-month intervention period, all subjects will receive the recommended standard of care concurrently with the assigned interventions.

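### Exclusion 10 exempts herpes zoster vaccine from its live-vaccine bar without limiting this to a non-live product, so a steroid-treated patient with a recent or planned live zoster vaccination is not excluded

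*Protocol*

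**What the plan says.** The Protocol's Exclusion section, criterion 10, bars a patient who "Received live vaccines within 12 weeks before randomization or anticipated to receive/require live vaccines during the study period, excluding herpes zoster vaccine". It has two limbs: live vaccines already given, with a 12-week look-back, and live vaccines expected or needed later. The zoster exemption follows both limbs and names no product type.

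Three other places bear on it:

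- Inclusion criterion 5 (Subjects Eligibility) reads "All subjects receiving concurrent treatment with steroids alone or in combination with antimalarial drugs". It gives no dose, duration or start date.
- The Intervention section adds that, over six months, "all subjects will receive the recommended standard of care concurrently with the assigned interventions". The drugs are not named.
- Exclusion criterion 8 bars "Current or recent (within 4 weeks before randomization) severe active or recurrent bacterial, viral, fungal, parasitic, or other infections", and herpes zoster is among the infections that it lists.

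**The concern.** The Protocol treats live vaccination, recent or planned, as a reason not to enrol. It also treats serious herpes zoster infection as a reason not to enrol. Yet it makes a single exception to the live-vaccine rule, and that exception is for zoster. In a population entirely on steroids, one would expect live zoster vaccine to be handled like any other live vaccine, or the exception to be justified.

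At stake is a safety screen. A site that follows the text would have no ground under criterion 10 to turn away or defer such a patient.

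**Working it through.** The Protocol attaches no figure to this point and no arithmetic applies. The check is a reading of the criteria against one another.

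**Step 1: what the exemption can act on.** Criterion 10 is confined to live vaccines, which leaves three situations.

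- *A live vaccine other than zoster:* barred, with or without the exemption.
- *A non-live zoster vaccine:* not barred, with or without the exemption, because the rule never reaches it.
- *A live zoster vaccine:* barred without the exemption, not barred with it.

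Only the third situation turns on the phrase. If the phrase has any effect, it is to admit recipients of live zoster vaccine.

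**Step 2: which limb it qualifies.** The phrase comes at the end, after both limbs, and is read here as applying to both. If it were attached to the second limb alone, the gap would be confined to planned vaccination. The remedy would be the same.

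**Step 3: whether another criterion closes the gap.**

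- Exclusion 8 names zoster, but as a disease: "infections (including but not limited to tuberculosis and atypical mycobacterial diseases, hepatitis B and C, HIV infection, herpes zoster". It turns on having a qualifying infection. A vaccination, past or planned, is not one.
- Exclusion 1 also mentions the vaccine, in "within 4 weeks before screening, except for herpes zoster vaccine". That clause is about biologics and targeted drugs. It contains a further exemption and imposes no restriction on vaccines.
- No other inclusion or exclusion criterion mentions vaccines, and nothing in the document limits the exempted product to a non-live, inactivated or recombinant one.

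**Step 4: whether a reason or condition is given.** None is. There is no rationale, no steroid dose below which a live zoster vaccine would be acceptable, and no minimum interval after vaccination.

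**Result.** On the text, a steroid-treated patient with a recent or expected live zoster vaccination passes criterion 10 and is stopped by nothing else that concerns vaccination.

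**The case against.** The best reply is that the authors meant a non-live product and added the phrase to reassure sites that zoster vaccination is no bar. Exclusion 1 lends this some support, because its own zoster exemption hangs on a list of drugs and appears to do nothing. The document thus does contain such a phrase without operative effect. This reading is plausible and cannot be ruled out. It does not rescue the wording: sites apply what is written, and if this was the intent, saying so costs nothing.

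A second reply is that the exception is deliberate and so a matter for the sponsor's judgement. That is possible too, but then a reason or a condition should accompany it, given that the same sentence bars every other live vaccine.

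A third reply concerns harm, and much of it stands. The document does not say that live zoster vaccine is dangerous with steroids, and it gives no steroid dose. For a past vaccination the steroid link is weaker still: the vaccine may have been given before steroids began, and exclusion at that point prevents no vaccination. What remains is an inconsistency within the Protocol's own safety logic.

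A reader might also infer that the Protocol authorises live zoster vaccination during the trial. It does not. Criterion 10 decides who enters and neither directs nor permits any vaccination afterwards.

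**Conclusion.** The point holds as a minor safety improvement to eligibility wording. Read literally, exclusion 10 admits patients with a recent or planned live zoster vaccination, and no other criterion stops them.

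Its size cannot be given. The document names no zoster product, states no steroid dose and offers no vaccination rate, so neither the number of patients affected nor the risk to each can be derived. It would be tempting to conclude that participants are exposed to a demonstrated hazard or that the trial's result is compromised. The documents support neither: they contain no evidence on vaccine risk, and nothing links the exemption to renal response at 24 weeks. Sample size, power and type I error are untouched.

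The conclusion rests on two assumptions: that sites apply the criterion as worded, and that both live and non-live zoster vaccines could be met in practice, which the document does not address. If only non-live products were in use, the phrase would be harmless and merely redundant.

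**What to change.** In exclusion criterion 10, do one of the following:

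- delete the closing exemption, so that live zoster vaccine falls under the general rule; or
- replace it with: *including live herpes zoster vaccine; non-live zoster vaccine is permitted*.

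The second is clearer for sites, because it settles both cases in words. If the sponsor does intend to admit recipients of live zoster vaccine, the criterion should say so and give the reason and any conditions.

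The change is one phrase. Its downside is that a few patients with a recent or planned live zoster vaccination would be excluded, or deferred by up to 12 weeks after vaccination. Recipients of a non-live zoster vaccine are unaffected, and no analysis changes.

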
## Intervention

In this study, the intervention factor is UC-MSCs. The UC-MSCs used in the study will be produced by Jiangsu Renocell Biotech Co., Ltd. that conforms to Good Manufacturing Practice standards. UC-MSCs at passages 4 will be utilized, and the transplantation dose will be 2 × 10^6^ /kg cells based on our preclinical study results. To ensure sterility and viability, UC-MSCs will be suspended in 30mL of sterile normal saline and stored at approximately 4 °C during transportation. The stem cell suspensions will be transported as quickly as possible to enable infusion within 12 hours of dissociation. Throughout the six-month intervention period, all subjects will receive the recommended standard of care concurrently with the assigned interventions.

## Safety indicators and primary and secondary efficacy endpoints

The primary efficacy endpoint of this study is the assessment of the overall response rate (complete response, CR, and partial response, PR) at 24 weeks, defined as a urine protein/creatinine ratio < 0.5, absence of active urinary sediment, and normal serum albumin level. The secondary efficacy endpoints include:

(1) Time to achieve PR and CR in both groups of subjects; (2) Changes in quantified urine protein and/or urine protein/creatinine ratio, serum albumin, serum creatinine, estimated glomerular filtration rate (eGFR), complement levels (C3, C4), autoantibodies (anti-dsDNA, ANA, anti-Smith, anti-RNP, anti-SSA/Ro, anti-SSB/La, anti-phospholipid antibodies) and Coombs test from the screening period to respective follow-up visits; (3) Changes in patient-reported Health Assessment Questionnaire (HAQ) scores and physician's Visual Analog Scale (PhGA-VAS) scores from the screening period to respective follow-up visits.(4) Changes in SLE Disease Activity Index-2000 (SLEDAI-2K), British Isles Lupus Assessment Group-2004 (BILAG-2004) scores, improvement rate in SLE Responder Index from the screening period to respective follow-up visits. (5) Overall response rate (CR + PR) in both groups of subjects at 12 weeks. The safety evaluation includes: (1) Recording of adverse events occurring from the start of subject enrollment until the end of follow-up; (2) Vital sign assessments (blood pressure, pulse, respiratory rate, and temperature) were evaluated every 4 weeks for 24 weeks; (3) Laboratory tests (including complete blood count, urinalysis, liver function, and blood biochemistry) were tested every 4 weeks for 24 weeks.

## Statistical analysis

Descriptive statistics will be used to summarize baseline characteristics, efficacy outcomes, and safety data. For the safety analysis set, all safety indicators will be obtained from those who have undergone UC-MSC. In the full analysis set, subjects will be excluded if they received no intervention or never gave any evaluation outcome. For the baseline characteristics, continuous variables will be expressed as means ± standard deviations, while categorical data will be given as frequencies. The paired *t*-test will be applied to analyze continuous and categorical variables. For the safety indicators, primary endpoint, and most secondary outcomes, including blood coagulation function, routine tests (blood, urine, and excrement), biochemistry and tumor findings, the paired *t*-test will be used to detect any differences. All statistical analyses will be performed using Statistical Product and Service Solutions (Version 22.0, IBM, New York, NY, USA) by the principal biostatistician. *p* < 0.05 will be considered statistically significant.

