# Umbilical cord mesenchymal stem (stromal) cells to treat lupus nephritis: protocol for a prospective clinical trial

## Study design

This is a proposed protocol for a prospective clinical trial, developed in accordance with the Standard Protocol Items: Recommendations for Interventional Trials (SPIRIT) checklist. The Affiliated Drum Tower Hospital of Nanjing University Medical School (Nanjing, China) acts as the initiating sponsor and coordinator of this trial. The observed group will receive intravenous infusion of Umbilical cord mesenchymal stem cells (UC-MSCs).

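### The safety analysis set is limited to UC-MSC recipients although the protocol implies a second group, so any excess harm over standard of care cannot be estimated from it

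*Protocol*

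**What the plan says.** The definition is in the protocol's Statistical analysis section: "For the safety analysis set, all safety indicators will be obtained from those who have undergone UC-MSC". The full analysis set, defined next, is not restricted in this way; it leaves out only patients with no intervention or no outcome evaluation. The same section names one test, the paired t-test, for the safety indicators, the primary endpoint and most secondary outcomes.

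Elsewhere the protocol points to a second group:

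- Safety indicators and primary and secondary efficacy endpoints lists "Time to achieve PR and CR in both groups of subjects" and "Overall response rate (CR + PR) in both groups of subjects at 12 weeks".
- Subjects Eligibility requires "fulfilling at least 4 out of the 11 ACR 1997 SLE classification criteria before randomization", and Exclusion bars those who "Received live vaccines within 12 weeks before randomization".
- Intervention says that "all subjects will receive the recommended standard of care concurrently with the assigned interventions".
- Study design assigns UC-MSC to what it calls the observed group.

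The endpoints section plans safety data as "Recording of adverse events occurring from the start of subject enrollment until the end of follow-up", with vital signs and laboratory tests every 4 weeks for 24 weeks. None of these items is limited to one group.

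**The concern.** Whether UC-MSC adds harm to standard of care is a central question for a trial of a cell product. Every patient here has biopsy-confirmed lupus nephritis, is on steroids at entry and receives standard of care. Infections, falls in blood counts and laboratory shifts can therefore be expected without UC-MSC. A set made up only of infused patients has no concurrent reference. A true excess could be dismissed as background, or background events could be blamed on the product.

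The rule also sits badly with the data plan. Adverse events are to be recorded from enrolment, yet events in a patient who is never infused, whichever group that patient belongs to, would not enter the safety set.

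**Working it through.** **1. Reading the sections together.** There is no figure in the plan to reproduce: the protocol states no sample size, allocation ratio or event rate.

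| Item | Protocol section | Limited to UC-MSC recipients? |
|---|---|---|
| Safety analysis set | Statistical analysis | Yes |
| Full analysis set | Statistical analysis | No |
| Adverse events, vital signs, laboratory tests | Safety indicators and endpoints | No group named |
| Time to response; 12-week response | Safety indicators and endpoints | No, both groups |
| Standard of care | Intervention | No, all patients |

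The number of patients without UC-MSC in the safety set is zero, whatever the trial size or allocation. A risk difference is p1 - p0, where p0 is the risk without UC-MSC. With no patients contributing to p0, the difference cannot be estimated from the set. A paired test does not fill the gap: by construction it compares paired values, most naturally two measurements on one patient, and it supplies no p0.

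**2. Illustration.** All counts are assumptions, chosen only to show the scale.

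*Infused patients only.* Suppose that 12 of 30 have an infection: 12/30 = 40%. The exact (Clopper-Pearson) 95% limits are the 2.5% point of Beta(12, 19) and the 97.5% point of Beta(13, 18), which are 0.227 and 0.594. The same 40% would be a doubling if the background rate were 20% and no excess if it were 40%. Nothing in the set says which background applies.

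*With 30 controls, 6 infected.* The difference is 12/30 - 6/30 = 0.40 - 0.20 = 0.20. The Wilson 95% limits are 0.246 to 0.577 for 12/30 and 0.095 to 0.373 for 6/30. Newcombe's limits are then:

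- lower: 0.20 - √[(0.40 - 0.246)² + (0.373 - 0.20)²] = -0.03
- upper: 0.20 + √[(0.577 - 0.40)² + (0.20 - 0.095)²] = 0.41

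Fisher's exact test gives p = 0.16.

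*With 30 controls, 12 infected.* The difference is 0, and the limits are ±√[(0.577 - 0.40)² + (0.40 - 0.246)²] = ±0.23.

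Both intervals (-3 to 41 points and -23 to 23 points) contain 0 and 20 points. At this assumed size a comparator yields an estimate with an interval, but does not by itself separate a doubling from no excess.

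**The case against.** The strongest objection is that the comparator is inferred. The protocol describes no control treatment, allocation method or ratio, and the Intervention section names only UC-MSC plus standard of care. In a single-arm trial, a safety set of infused patients would be ordinary. This stands as a limit on the point but does not remove it: the references to two groups and to randomization would then be wrong, so the sections need reconciling either way.

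Second, a reader might infer that control safety data are discarded or never collected, or that no harm can be assessed at all. The document does not support that. The data lie outside a named analysis set, the endpoints section appears to plan their collection, and within-patient changes can be described. The Statistical analysis section also opens by promising descriptive summaries of safety data without restricting them to one group. That sentence leaves room for a table of the other group, but it does not override the more specific set definition that follows and it names no comparison between groups.

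Third, a reader might take the paired t-test to be explicitly a before/after test in treated patients. The protocol says neither. Its use across all endpoints is a separate matter and adds no weight here beyond the fact that no other safety test is named.

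Fourth, tabulation by group is commonly left to an SAP, and one may exist. That would answer an omission. Here the protocol states a definition, and an SAP that included the second group in the safety set would contradict it.

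**Conclusion.** The point holds, conditional on a concurrent comparator. If there is one, the stated safety set excludes it entirely, and any excess harm of UC-MSC over standard of care cannot be estimated from that set. If there is none, the safety set is acceptable and the wording on groups and randomization is what must change.

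The conclusion rests on the set definition and not on the illustration, whose counts are assumed. It would be tempting to say that the control data would settle whether harm is raised; at 30 per group they would not, as the intervals above show. What is lost is the ability to estimate the excess and state its uncertainty. The primary efficacy endpoint is not affected by this definition.

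**What to change.** State in Study design whether there is a concurrent comparator and, if so, what it receives. Then bring the eligibility, intervention, endpoint and analysis sections into line with that statement.

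If there is a comparator:

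- define the safety set as all patients who received any assigned study treatment, including standard of care alone, analysed by treatment received;
- report adverse events, serious adverse events and infections by group, with risk differences and 95% CIs;
- keep a separate table of UC-MSC recipients for infusion reactions.

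The cost is a few sentences and extra table columns. This assumes that adverse events, vital signs and laboratory tests are collected in both groups on the same schedule, as the endpoints section appears to plan; the protocol should say so explicitly, because the safety items name no group.

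### The only inferential test named is a paired t-test, which cannot compare the two groups and does not suit the response-rate and time-to-response outcomes

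*Protocol*

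**What the plan says.** The Protocol's Statistical analysis section names one test: "The paired *t*-test will be applied to analyze continuous and categorical variables". The sentence after it turns to outcomes and states that "the paired *t*-test will be used to detect any differences". Its scope is wide: "For the safety indicators, primary endpoint, and most secondary outcomes, including blood coagulation function, routine tests (blood, urine, and excrement), biochemistry and tumor findings". No between-group, categorical-data or survival method appears.

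The endpoint section lists outcomes of several kinds:
- changes in laboratory values and scores, measured "from the screening period to respective follow-up visits";
- two rates: "Overall response rate (CR + PR) in both groups of subjects at 12 weeks" and "improvement rate in SLE Responder Index from the screening period to respective follow-up visits";
- a time-to-event outcome: "Time to achieve PR and CR in both groups of subjects".

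Two of these are expressly for both groups. The eligibility criteria refer to randomization. The Intervention section refers to assigned interventions and gives all subjects standard of care throughout the six-month period.

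**The concern.** A paired t-test compares each patient with himself or herself. It asks whether the mean change differs from zero, not whether the change is larger with UC-MSCs than without. Since everyone receives standard of care, some change is expected in any case. For proteinuria, entry above a threshold adds an apparent fall through regression to the mean.

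The test also needs two measurements of the same quantity. A response rate has no informative screening value, and time to response has none at all. Applied as written, the rule could produce small p-values for secondary outcomes, and for the primary endpoint, that carry no information about UC-MSCs.

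**Working it through.** The Protocol gives no sample size, effect size, SD or response rate, so it has no figure to reproduce. The sample sizes, shifts and rates below are assumptions. Tests are taken as two-sided at 0.05; the Protocol states the 0.05 but not the sidedness.

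**Continuous outcomes.** Let δ be the mean change from standard of care alone, in SDs of the change, with no UC-MSC effect. The paired test is significant with probability P(|T| > c), where T is noncentral t with n − 1 degrees of freedom and noncentrality δ√n, and c is the 97.5% point of the central t.

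| n | c | δ = 0.3 | δ = 0.5 | δ = 0.8 |
|---|---|---|---|---|
| 20 | 2.093 | 0.247 | 0.565 | 0.924 |
| 30 | 2.045 | 0.355 | 0.754 | 0.988 |

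For example, at n = 30 and δ = 0.5 the noncentrality is 0.5 × √30 = 2.739. Simulation (20,000 trials per setting) agrees: 0.246, 0.567, 0.924 at n = 20 and 0.351, 0.757, 0.989 at n = 30. In the same simulated trials, with equal change in both arms, a between-arm t-test on the change was significant in 4.7% to 5.3% across all settings, including n = 50 per arm.

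**Response rates.** Entry requires a urine protein/creatinine ratio or 24-hour protein above 1.0; response requires a ratio below 0.5. Nearly every patient is therefore a non-responder at screening. The SLE Responder Index outcome is an improvement from screening, so nobody can have met it at screening. The differences are then 1 for r responders and 0 for the rest, and with p = r/n

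t = √[(n − 1) p / (1 − p)].

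- n = 30, r = 3: t = √(29 × 3/27) = 1.795, p-value 0.083.
- n = 30, r = 4: t = √(29 × 4/26) = 2.112, p-value 0.043.
- Four responders also suffice at n = 20 (p-value 0.042) and n = 100 (0.045).
- The exact McNemar p-value for four changes, all in one direction, is 2 × 0.5⁴ = 0.125.

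The test thus asks only whether the response rate exceeds zero. At n = 30, the chance of at least four responders when standard of care alone gives a rate of 10%, 20% or 30% is 0.353, 0.877 or 0.991.

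**Proteinuria.** Regression to the mean was simulated for log protein/creatinine ratio with no treatment effect: log SD 0.7, correlation between visits 0.6 to 0.9, source geometric mean 1.0 to 2.0, entry above 1.0. The apparent fall is 2% to 20%, and the paired test at n = 30 is significant in 6.5% to 53% of trials. The simulation selects on the ratio alone. The Protocol also admits patients on 24-hour protein, so these figures probably overstate the effect on the ratio.

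**Time to PR and CR.** No arithmetic applies. There is no screening value to pair with, and patients who have not responded by their last visit have no observed time.

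**The case against.** Much of the case on the other side limits the claim without removing it.

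- **The blanket sentence follows the one on baseline characteristics and may have been meant for baseline data.** Possible, but the next sentence assigns the same test to outcomes.
- **A reader might infer that time to PR and CR will be t-tested in responders only.** The text says most secondary outcomes and does not expressly assign that one. What stands is that the section offers no method that suits it.
- **What is paired is not stated.** Pairing with the screening value is inferred from how the endpoints are defined.
- **A reader might infer that the test is invalid for all categorical data.** That is too strong. For a binary variable that can change both ways, it approximates McNemar's test in large samples, although the question remains within-patient. The Protocol speaks of BILAG-2004 scores, not grades, and does not say whether autoantibodies are recorded as status or level. The firm examples are SLE Responder Index response and the 12-week rate.
- **A reader might infer that nearly every secondary outcome would come out significant.** This is not shown; the probability runs from 0.25 to 0.99 over the assumed shifts at n = 20 to 30.
- **Regression to the mean might look like a second defect.** It bears directly only on proteinuria, and randomized groups share it. It needs no separate remedy.
- **The trial may be single-arm.** The study design section describes only an observed group and no comparator, whereas other sections speak of both groups and randomization. A paired test would then be possible for continuous change, but its p-value still could not separate UC-MSCs from standard of care.

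An unseen SAP does not answer the point, because the Protocol itself fixes the test.

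**Conclusion.** Wrong as written. The Protocol commits to a within-patient test for outcomes that it defines for two groups, and names nothing that compares them. The size depends on how far standard of care moves each outcome. Over assumed shifts of 0.3 to 0.8 SD, the chance of significance without any UC-MSC effect is 25% to 92% at n = 20 and 36% to 99% at n = 30, against about 5% for a between-group test. For response rates, four responders are enough at each sample size shown.

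The conclusion about which question the test answers rests on the text alone; only the percentages rest on assumptions. The same sentence covers the primary endpoint and the safety indicators, so the defect is wider than the secondary outcomes and should be corrected for all of them together.

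**What to change.** First confirm in the Protocol that the trial has two arms. If so, replace the paired t-test with between-group comparisons:

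- **Continuous outcomes and scores:** change or follow-up value adjusted for the baseline value, by ANCOVA or a repeated-measures model.
- **Binary outcomes** (response at 12 and 24 weeks, SLE Responder Index response): difference in proportions with a confidence interval.
- **Time to PR and CR:** Kaplan-Meier with log-rank or Cox, with non-responders included as censored.
- **Baseline tables:** descriptive only.

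If the trial is in fact single-arm, report estimates with confidence intervals and draw no efficacy conclusion from within-arm p-values.

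The cost is analysis wording only. No additional sample or visit is needed.
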